## Abstract

Malnutrition is an escalating concern in low-and-middle-income countries (LMICs), including Ecuador, particularly within rural settings. To address this issue, food forests emerge as a promising intervention. This research protocol outlines a controlled intervention in the province of Santa Elena, aiming to evaluate the efficacy of a food forest in enhancing nutritional outcomes, with potential implications for broader replication. The study will be conducted in the Colonche Parish of Santa Elena Canton, where one commune will be randomly selected to receive the food forest intervention. In contrast, another similarly characterized commune, also randomly selected through cluster-based sampling, will serve as a control group, receiving no intervention. This randomized, comparative approach will enable a more precise assessment of the food forest's impact. Data collection will occur at three intervals: baseline, 6 months, and 12 months post-intervention. Comprehensive questionnaires will be employed to measure the food forest's influence on the communities' nutritional, economic, and health metrics, distinguishing between the intervention and control communes to elucidate the intervention's specific effects.

## 1 Introduction

Malnutrition is a severe global challenge, particularly in low- and middle-income countries (LMICs), where it causes ~3.1 million child deaths annually, representing nearly 45% of all child fatalities (1–5). Poor nutrition in the early years of life, especially in vulnerable populations, can lead to long-term adverse effects such as impaired cognitive and motor development, poor educational outcomes, reduced work capacity, and lower adult economic productivity (4, 6–11). Among the poorest communities, particularly in rural areas, malnutrition is compounded by socioeconomic constraints, forcing families to rely on cheaper, ultra-processed foods at an increasingly early age. This shift in dietary habits, influenced by factors such as population growth, fluctuating food prices, political instability, and environmental changes, places further pressure on the global food system and intensifies the complexity of addressing malnutrition (12–16).

To effectively combat child malnutrition, both nutrition-specific interventions, such as supplementation, and broader strategies, including agricultural improvements and social safety nets, are necessary (17–19). These methods not only address immediate causes, like nutrient deficiencies, but also tackle underlying issues related to income and food access. Forest ecosystems, for example, play a vital role in food security, particularly in rural LMICs, where forest-derived foods such as fruits, vegetables, meat, and fish meet a significant portion of dietary needs (20). A study of 24 countries found that more than 55% of rural households with moderate access to forest resources obtain food from the forest (20). Another study in Cameroon found that women in rural forest-dependent communities obtained 93% of their daily vitamin A from forest food (21).

In addition to providing direct food sources, forests also serve as important sources of income through the sale of timber and non-timber products. Research, including a review by Vedeld et al. of 51 case studies, indicates that forest products account for about 22% of these households' total income (22, 23). This additional income is frequently reinvested in food security and health, helping to safeguard nutrition and prevent nutrition-related diseases (23, 24).

Building on this foundation, Food Forests offer a promising intervention by combining ecological sustainability with agricultural productivity. These diverse, multi-layered systems go beyond traditional forestry, providing food, livelihood opportunities, and environmental benefits (25–29). Evidence from a case study in Sangthong district, Laos, illustrates the potential of Food Forests, where even less affluent families significantly improved their dietary quality through integrated agroforestry systems (30). Despite these promising indicators, however, there is a notable gap in the literature, as few comprehensive studies have rigorously quantified the impact of Food Forest interventions on nutritional, economic, and health outcomes, with most existing research being qualitative or retrospective in nature (31, 32).

The present study aims to address this gap by evaluating the impact of a Food Forest initiative on the nutritional status, socioeconomic conditions, and health outcomes of rural communities in the Colonche Parish of Santa Elena Province, Ecuador. Using a randomized, controlled trial design, this research will provide empirical evidence on the effectiveness of Food Forests as a solution to malnutrition and poverty. The findings from this study have the potential to inform similar initiatives in rural settings across Latin America and other LMICs, fostering socioeconomic development and environmental sustainability.

## 2 Objectives

### 2.1 Main objective

To evaluate the impact of the Food Forest initiative on nutritional status, socioeconomic conditions, and health outcomes in rural communities in a developing country, using the Colonche Parish, Santa Elena Province, Ecuador, as a case study.

### 2.2 Specific objectives

To determine the effect of the Food Forest initiative on dietary diversity, malnutrition rates, and overall nutritional status of participating communities.To analyze changes in household income levels, employment opportunities, and economic stability as a result of the Food Forest activities.To examine the influence of the Food Forest initiative on physical and mental health, including general health perception, physical functionality, and emotional wellbeing among participants.

## 3 Methods

### 3.1 Study design

This study employs a randomized community trial design to assess the impact of a novel Food Forest reforestation technique that emphasizes the use of endemic and food-producing species. The goal is to enhance food sovereignty among coastal families in the Santa Elena Province, Ecuador. This initiative, a collaborative effort by Nedetel and CECAPROF Corporación Ecuatoriana De Capacitación (two companies that serve the area), aims to address the dual challenges of malnutrition and low average family incomes in the region (33). Participants for the study will be recruited from rural areas within the Colonche Parish of the Santa Elena Canton, a geographical area detailed in Figure 1 (34, 35). The study randomly allocated one commune to receive the Food Forest intervention, while a similarly characterized commune was randomly assigned as a control group, receiving no intervention. This randomization process ensures that the study meets the criteria of a randomized community trial. In consideration of ethical concerns, we have planned a delayed intervention for the control group. After the study period, the control commune will also receive the food forest intervention, contingent on securing additional funding. This phased approach allows for a scientifically rigorous assessment of the intervention's effects while ensuring that both communities ultimately benefit from the food forest initiative. The intervention strategy was developed based on insights from prior research, supplemented by consultations and interviews with experts in nutrition and reforestation, ensuring that the Food Forest initiative is ecologically viable and tailored to meet the nutritional and economic needs of the local communities involved.

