### 3.3 Sampling

In our study within Colonche Parish, we will engage in a randomized selection process to choose one commune for the treatment group, where the Nutritional Forest will be implemented, and two communes for the control group, which will not have access to the Nutritional Forest. This selection process will encompass all communes of the Parish, including Aguadita, Ayangue, Bajadita de Colonche, Bambil Collao, Bambil Desecho, Calicanto, Cerezal Bellavista, Febres Cordero, Jambelí, Las Balsas, Loma Alta, Manantial de Guangala, Manantial de Colonche, Monteverde, Palmar, Río Seco, Salanguillo, and San Marcos. Each commune will be treated as an individual cluster, and a random cluster sampling method will be employed to ensure a fair and unbiased selection of the communes for both the treatment and control groups.

The random selection will be carried out using a lottery system where each commune will be assigned a unique identifier, and a computerized random number generator will select the treatment commune and control communes. This approach minimizes selection bias and ensures a randomized, equitable process.

The 1:2 allocation ratio (one treatment commune and two control communes) was chosen due to feasibility considerations and community input. The local community expressed a preference for starting the Nutritional Forest intervention in one commune initially, allowing for more focused implementation and monitoring. This also aligns with the available resources and ensures that the intervention can be tailored to the specific needs of the treatment community.

Following the selection of the commune, we will proceed to sample households within each of the chosen commune. Household selection will be conducted using a two-stage sampling method. First, a list of households within each commune will be obtained from local community records. Second, a systematic sampling method will be applied to randomly select households from this list, ensuring that the sample is representative of the entire community. This step will ensure that our assessment captures a broad spectrum of community experiences and perspectives regarding the impact of the Nutritional Forest intervention.

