### 3.10 Statistical analysis

All statistical analyses will be performed using Stata 18.0 (44). Descriptive statistics will be calculated for both qualitative (e.g., categorical) and quantitative (e.g., continuous) data. Categorical variables, such as employment status or food security, will be summarized using frequencies and percentages, while continuous variables, such as household income or nutritional status (e.g., BMI), will be described using means and standard deviations for normally distributed data, or medians and interquartile ranges for non-normally distributed data.

For hypothesis testing, categorical variables like food security (measured as secure/insecure) and employment status (e.g., employed/unemployed) will be compared between the intervention and control groups using Chi-square tests or Fisher's exact tests, depending on sample sizes. For continuous variables, such as changes in household income or nutritional status (e.g., BMI, dietary diversity scores), Student's *t*-tests will be used if the data are normally distributed. If normality assumptions are violated, Mann-Whitney U tests will be applied instead.

To evaluate changes over time within the same group (e.g., baseline to 6 months), paired *t*-tests will be used for normally distributed continuous variables, such as income or BMI, while Wilcoxon signed-rank tests will be used for non-normally distributed variables. For categorical variables like food security status over time, McNemar's test will be applied.

Regarding regression models, linear regression will be used to assess continuous outcomes such as household income levels, nutritional status (BMI), or dietary diversity scores. Logistic regression will be applied to binary outcomes, such as food security (secure/insecure) or whether participants report improved health (yes/no). For outcomes with multiple categories, such as levels of health perception (good, fair, poor) or employment status (employed, unemployed, seeking work), multinomial logistic regression will be used.

To account for repeated measures over time (e.g., baseline, 6 months, and 12 months post-intervention), mixed-effects models (both linear and logistic) will be employed. These models will allow us to assess the effect of the intervention across different time points while controlling for intra-individual correlations. All hypothesis tests will be two-tailed, and a *p* < 0.05 will be considered statistically significant.

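### One treated commune against one or two controls confounds the forest with the commune, so the randomised-trial claim and the p<0.05 arm tests are not supported

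*Protocol article*

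**What the plan says.** Whole communes are allocated, and one is treated. Section 3.1 of the protocol article has one control: "The study randomly allocated one commune to receive the Food Forest intervention, while a similarly characterized commune was randomly assigned as a control group". The Abstract agrees: "another similarly characterized commune, also randomly selected through cluster-based sampling, will serve as a control group, receiving no intervention". Section 3.3 has two: "The 1:2 allocation ratio (one treatment commune and two control communes) was chosen due to feasibility considerations and community input". It draws them by computerised lottery from all 18 listed communes of the parish and states no matching or restriction.

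Section 3.3 recognises the commune as the cluster, but only for selection: "Each commune will be treated as an individual cluster, and a random cluster sampling method will be employed". From this, section 3.1 concludes: "This randomization process ensures that the study meets the criteria of a randomized community trial".

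Section 3.10 then compares arms on family and individual data. Categorical variables "will be compared between the intervention and control groups using Chi-square tests or Fisher's exact tests, depending on sample sizes". Continuous variables get t-tests or Mann-Whitney tests, followed by linear, logistic and multinomial regression. Mixed models are added for repeated measures: "These models will allow us to assess the effect of the intervention across different time points while controlling for intra-individual correlations". One threshold covers everything: "All hypothesis tests will be two-tailed, and a *p* < 0.05 will be considered statistically significant".

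**The concern.** Inference about an intervention given to whole communes rests on variation between communes in the same arm. With a single treated commune, the indicator for the forest and the indicator for that commune are the same variable. The lottery makes the choice of commune fair, but it cannot average out differences between communes when only one is drawn for treatment.

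The tests in 3.10 treat families and individuals as if each had been allocated separately. The only correlation that the mixed models are said to handle is within a person over time. A local change in prices, jobs, weather or services in one commune can therefore produce a small p-value that is read as a forest effect. At stake is the Introduction's promise of evidence on effectiveness that could guide similar programmes elsewhere. The reported error rate would not be the stated 5%.

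**Working it through.** **The plan's own figure.** Section 3.4 uses Z = 1.96, p = 0.5, E = 0.05 and N = 968 families. n0 = 1.96² × 0.25 / 0.05² = 384.16. With finite population correction, 384.16 / (1 + 383.16/968) = 275.2, rounded up to 276. Both figures reproduce; 300 allows for attrition. This is the precision of one proportion in one commune. No arm contrast, number of communes or between-commune variance enters it.

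**Inputs for the check.** m = 300 families per commune (3.4); two-sided alpha 0.05 (3.10); 1 vs 1 (Abstract, 3.1) or 1 vs 2 (3.3) communes. The ICC is not in the article, so 0.001 to 0.05 is an assumed range. It is the commune share of variance for whatever is tested, whether outcome or change. One observation per family and SD = 1 are assumed.

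**Step 1: type I error when the commune is ignored.** Design effect DE = 1 + (m − 1) × ICC = 1 + 299 × ICC. True type I error = 2 × [1 − Φ(1.96/√DE)].

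| ICC | DE | 1.96/√DE | True type I error |
|---|---|---|---|
| 0.001 | 1.30 | 1.72 | 8.5% |
| 0.005 | 2.50 | 1.24 | 21% |
| 0.01 | 3.99 | 0.98 | 33% |
| 0.05 | 15.95 | 0.49 | 62% |

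Simulation with 20,000 replicates per setting gave 8.6–8.7%, 21–22%, 33–34% and 63%, nearly the same for 1 vs 1 and 1 vs 2. The nominal 5% is right only at ICC = 0.

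**Step 2: can more families help?** No. As m grows, the standard error (SE) of the contrast falls only to √(2 × ICC) for 1 vs 1 and √(1.5 × ICC) for 1 vs 2. At ICC 0.01 these floors are 0.14 and 0.12 SD.

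**Step 3: the commune as the unit.**
- 1 vs 1: 2 communes − 2 = 0 degrees of freedom, so between-commune variance cannot be estimated. The two-sided permutation p is always 1.
- 1 vs 2: 3 − 2 = 1 degree of freedom, critical t = 12.71. There are three possible allocations, so the smallest permutation p is 1/3. At ICC 0.01 a commune mean has variance 0.01 + 0.99/300 = 0.0133. The SE is √(0.0133 × 1.5) = 0.141, and the 95% half-width is 12.71 × 0.141 = 1.8 SD.

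A commune random effect added in an analysis plan meets the same 0 or 1 degree of freedom.

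**Step 4: what an interval over an ICC range would show.** With the ICC taken as known, half-width = 1.96 × √[(ICC + (1 − ICC)/300) × c], where c = 2 for 1 vs 1 and 1.5 for 1 vs 2.

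| ICC | 1 vs 1 (SD) | 1 vs 2 (SD) |
|---|---|---|
| 0 | 0.16 | 0.14 |
| 0.001 | 0.18 | 0.16 |
| 0.005 | 0.25 | 0.22 |
| 0.01 | 0.32 | 0.28 |
| 0.05 | 0.64 | 0.55 |

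**Step 5: one treated commune, controls spread as 10 communes × 60 families, ICC 0.01.** A control-commune mean has variance 0.01 + 0.99/60 = 0.0265. A commune-level t interval with 9 degrees of freedom has half-width 2.26 × √(0.0265 × 1.1) = 0.39 SD. The smallest permutation p is 1/11 = 0.091. Even against all 17 other communes it is 1/18 = 0.056.

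**The case against.** The strongest reply is that the study has a baseline and repeated measures, and that 3.10 plans mixed models across time points. A contrast of changes removes stable differences between communes, so the type I errors above apply to it only if change scores carry such ICCs. That is right, and at ICC 0.001 the inflation is modest. But changes specific to one commune remain, and section 4.3 itself names weather as an outside influence.

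A second reply is that section 2.1 frames Colonche as a case study and that 3.3 justifies one forest by resources and community preference. That explains the design, but it does not support the sentence in 3.1 or the p<0.05 rule.

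A third is that an unseen analysis plan may handle clustering. It could add a commune term, but it could not create the missing degrees of freedom.

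A reader might also infer more than the article supports:
- That any local difference will come out as a significant forest effect. The error rates above show that it can, not that it will.
- That allocation was not random. The described lottery is genuine randomisation of communes; what is lacking is replication.
- That every planned p-value is invalid. Paired and McNemar tests describe change within a group; they do not attribute it to the forest.
- That the communes are plainly unalike. All lie in one parish, and 3.2 gives about 3,875 people and 968 households for each. The narrower point stands: an unrestricted lottery does not secure the similarity that the Abstract and 3.1 assert.

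**Conclusion.** The point holds with either one or two control communes. The forest is fully confounded with the treated commune, the sentence in 3.1 claims more than the design can give, and p<0.05 for the arm contrast in 3.10 does not have a 5% error rate unless communes differ by nothing at all.

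How far the error rate exceeds 5% depends on an ICC that the article does not state: from about 8.5% at 0.001 to about 62% at 0.05, with 300 families per commune. The absence of usable commune-level inference (0 or 1 degree of freedom) does not depend on the ICC. The conclusion concerns between-arm p-values read as a forest effect; estimates of change in the named communes remain worth reporting.

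**What to change.** **Needed; costs wording and analysis only.**
1. Reconcile one control commune (Abstract, 3.1) with two (3.3).
2. Replace the sentence in 3.1 with: a controlled before-after comparison of the named communes, with the treated commune chosen by lottery.
3. In 3.10, drop p<0.05 effectiveness claims for the arm contrast. Report difference-in-change estimates with intervals shown over a stated ICC range, as in Step 4.
4. Remove the statement that the communes are alike in character, unless the lottery is restricted to comparable communes.

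**Optional; only if allocation has not yet been done and the sponsor accepts the cost.** Section 3.1 describes allocation in the past tense and 3.3 in the future tense, so this must be established first. Keep one forest and spread the control interviews over more communes, for example 10 × 60, with a commune-level t interval: about 0.39 SD half-width at ICC 0.01, against about 1.8 SD for 1 vs 2. The t interval assumes similar variance across communes and has to carry the inference, because a permutation test there cannot go below 1/11.

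This option is not free. More communes would come under the control-group support (3.11) and delayed-forest undertakings (3.1, 3.11). The 600 control interviews are unchanged only under the two-control version (2 × 300); under the one-control version they double from 300. Using about ten control communes also pulls against restricting the lottery to comparable ones, since the article does not show that enough of these exist.

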**Figure 1 F1:**
[figure not shown]
Political division of the Colonche Parish. Source: Rural Parochial Decentralized Autonomous Government of Colonche (34).

### 3.2 Participants and recruitment

The focus of this study is on the residents of a specific commune within the Colonche Parish, located in the Santa Elena province of Ecuador. The participant pool consists of families with an average monthly income of $463.93, a figure significantly lower than the cost of the Ecuadorian basic necessities basket, estimated at $789.57 (36, 37). The predominant educational attainment among community members is up to the primary level, facilitated by the region's publicly funded educational system. Each commune is home to ~3,875 individuals, distributed across 968 households. In addressing the needs of this community, the study aims to provide direct access to food for all participating families, leveraging the coastal commune's resources to enhance their food security and nutritional wellbeing.

### 3.3 Sampling

In our study within Colonche Parish, we will engage in a randomized selection process to choose one commune for the treatment group, where the Nutritional Forest will be implemented, and two communes for the control group, which will not have access to the Nutritional Forest. This selection process will encompass all communes of the Parish, including Aguadita, Ayangue, Bajadita de Colonche, Bambil Collao, Bambil Desecho, Calicanto, Cerezal Bellavista, Febres Cordero, Jambelí, Las Balsas, Loma Alta, Manantial de Guangala, Manantial de Colonche, Monteverde, Palmar, Río Seco, Salanguillo, and San Marcos. Each commune will be treated as an individual cluster, and a random cluster sampling method will be employed to ensure a fair and unbiased selection of the communes for both the treatment and control groups.

The random selection will be carried out using a lottery system where each commune will be assigned a unique identifier, and a computerized random number generator will select the treatment commune and control communes. This approach minimizes selection bias and ensures a randomized, equitable process.

The 1:2 allocation ratio (one treatment commune and two control communes) was chosen due to feasibility considerations and community input. The local community expressed a preference for starting the Nutritional Forest intervention in one commune initially, allowing for more focused implementation and monitoring. This also aligns with the available resources and ensures that the intervention can be tailored to the specific needs of the treatment community.

Following the selection of the commune, we will proceed to sample households within each of the chosen commune. Household selection will be conducted using a two-stage sampling method. First, a list of households within each commune will be obtained from local community records. Second, a systematic sampling method will be applied to randomly select households from this list, ensuring that the sample is representative of the entire community. This step will ensure that our assessment captures a broad spectrum of community experiences and perspectives regarding the impact of the Nutritional Forest intervention.

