## 4 Interventions and procedures

### 4.1 Development of intervention

The procedures of the intervention were developed through the consultation of experts linked to the two organizations, together with the planning of the members of the organizations themselves, in such a way that previous experiences related to the subject have been considered together with a literary review. However, the development objectives were considered in terms of economic, environmental, and health themes.

Community involvement is central to both the establishment and maintenance of the food forest. The land designated for the food forest is community-owned, allowing the benefits of the forest to be shared among all members. To ensure long-term sustainability, community members will be actively engaged in both planting and maintaining the forest. Training in agroecology and sustainable practices will be provided by CECAPROF and Nedetel, who will supply the necessary seeds and inputs, such as organic fertilizers and tools. Additionally, regular workshops will be conducted to educate the community on agroecological methods, fostering a collaborative environment where community members collectively manage the food forest, including planning, harvesting, and distribution of yields.

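### The control commune is described as similar to the treated one, but the only selection rule is an unrestricted lottery over all 18 communes, so the design does not secure that similarity

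*Protocol article*

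**What the plan says.** The comparability claim appears twice in the Protocol article. The Abstract says that "another similarly characterized commune, also randomly selected through cluster-based sampling, will serve as a control group". Section 3.1 repeats it in the past tense: "a similarly characterized commune was randomly assigned as a control group, receiving no intervention".

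The rule that is meant to produce this control is in section 3.3. The frame is the whole parish: "This selection process will encompass all communes of the Parish, including Aguadita", followed by 17 further names, 18 in all. The mechanism is a lottery in which "a computerized random number generator will select the treatment commune and control communes". Each commune is one cluster. Section 3.3 allocates one treated and two control communes, whereas the Abstract and section 3.1 have one control; that discrepancy is a separate matter, and both cases are covered below. No commune-level eligibility condition, stratum, matching variable or restriction on the draw is stated.

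On the target population, section 3.1 says: "The goal is to enhance food sovereignty among coastal families in the Santa Elena Province, Ecuador". Section 3.2 refers to the resources of the coastal commune and gives one size for all: "Each commune is home to ~3,875 individuals, distributed across 968 households". Section 4.1 adds: "The land designated for the food forest is community-owned, allowing the benefits of the forest to be shared among all members".

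**The concern.** A stated property and a stated procedure do not fit together. A lottery over every commune in the parish is a legitimate way to allocate, but it does not make the drawn communes alike. Randomisation balances clusters only in expectation over many units. Here one commune is treated and one or two are controls, so a single draw fixes any commune-level difference in baseline diet, income and food access.

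What is at stake is interpretation. The similarity wording is the protocol's main assurance that the comparator is fair, and it would be cited in support of any difference between communes. Sampling 300 families per commune (section 3.4) makes each commune's mean more precise, but it does nothing to make the communes comparable. The setting adds to the tension: the text describes a coastal population, while the frame is not restricted by setting.

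**Working it through.** **Set side by side.**
- Property claimed (Abstract, 3.1): the control resembles the treated commune and was randomly chosen.
- Procedure stated (3.3): identifiers for all communes, computerised random selection, no restriction.
- Possible basis for similarity (3.2): one size, one average family income and one predominant education level. None of these is used as a selection criterion.

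**Size of the draw.** The plan attaches no figure to similarity, so there is none to reproduce. Counting the names in 3.3 gives 18 communes. With one treated and two controls there are 18 × C(17,2) = 18 × 136 = 2,448 possible allocations; with one control, 18 × 17 = 306. Under the stated rule all are equally likely, and none is excluded for dissimilarity.

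**Illustration.** Let c of the 18 communes be coastal. The document does not give c, so 4, 6 and 9 are assumed.

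One control: P(type differs) = 1 − [C(c,2) + C(18−c,2)] / C(18,2), with C(18,2) = 153.
- c = 4: 1 − (6 + 91)/153 = 56/153 = 37%
- c = 6: 1 − (15 + 66)/153 = 72/153 = 47%
- c = 9: 1 − (36 + 36)/153 = 81/153 = 53%

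Two controls: P(at least one differs from the treated commune) = 1 − [C(c,3) + C(18−c,3)] / C(18,3), with C(18,3) = 816.
- c = 4: 1 − (4 + 364)/816 = 448/816 = 55%
- c = 6: 1 − (20 + 220)/816 = 576/816 = 71%
- c = 9: 1 − (84 + 84)/816 = 648/816 = 79%

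Any two-level trait with the same counts gives the same numbers. Restricting the draw to one type makes the mismatch on that trait zero by construction, and on that trait only.

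**The case against.** The strongest reply is that unmatched randomisation of clusters is legitimate, that the article condenses a fuller protocol, and that the similarity wording may be loose shorthand for communes of one parish with a common size, low income and mostly primary education. Part of this stands: matching is a choice, and its absence alone would be no fault. But section 3.3 sets out the frame, the mechanism and the ratio, so this is not merely an omitted detail. The rule as stated does not deliver the property as stated. The common description in 3.2 is not a selection rule, and the one figure it gives for every commune concerns size.

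It is also fair to say that the coastal wording may describe the region rather than a subset of communes. No text classes any commune as inland, and the map is not shown. The percentages therefore illustrate and do not measure.

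A reader might infer more than the document supports:
- *That a drawn commune without land would have to be redrawn, ending random allocation.* No redraw is described. Section 4.2.1 places the 15 hectares only within the parish. It gives the commune exclusive rights to the land, so a local site is plausible, but it is not stated. Section 4.1 does not say when the land was designated or in which commune.
- *That some commune is too small to supply 300 families.* The only figure given is about 968 households per commune.
- *That the communes differ in livelihood, for instance fishing against farming.* Nothing in the document says so.

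Finally, matching cannot cure the larger problem that one treated commune is inseparable from its intervention. That is correct, and it limits how much weight this point should carry.

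**Conclusion.** The point holds as an internal conflict: the Abstract and section 3.1 assert a comparability that the lottery in section 3.3 does not produce. The mismatch between the coastal wording and the unrestricted frame supports it but is weaker. The size cannot be determined from the document. The illustrative range is 37% to 53% with one control and 55% to 79% with two, conditional on 4 to 9 coastal communes out of 18 and on setting mattering for the outcomes.

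This should be corrected because it bears on what the trial may claim about its comparator, but it ranks below the faults that must be fixed before the trial can proceed. It does not show that the allocation was not random, that the forest cannot be sited, or that the household sample cannot be reached.

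**What to change.** **If the draw has not been made** (section 3.3 uses the future tense), revise 3.3 as follows:
1. Before the draw, screen all 18 communes on the same criteria for both arms: the setting that the target population requires, enough listed households for the sample of 300, and community-owned land usable for the forest. The land criterion belongs to both arms because sections 3.1 and 3.11 plan a later forest for controls.
2. From the eligible communes, use existing records to form a set similar in size, setting and income.
3. Randomise within that set which commune receives the forest.

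**If the draw has been made** (section 3.1 uses the past tense), remove the similarity wording from the Abstract and 3.1, report the drawn communes' characteristics side by side, and state that comparability was not secured by design.

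The first option costs protocol wording and a desk review of 18 communes. Its downside is a narrower frame, so the result applies to communes of that type. The second costs wording and one descriptive table. Either way, the text should say that similarity on a few recorded features reduces but does not remove the confounding of commune with intervention.
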